### Participant timeline

After a clear decision to conduct diagnostic angiography for CCS patients based on current guidelines [22,23]. They will be informed about the study and available options. After providing the informed consent, the pre-PCI questionnaire will be completed by an interventional cardiologist and a member of TMC. Patients will be randomized to treatment or control group after diagnostic angiography and before stent insertion. The loading dose of the assigned medications for each group will be administered to the patient prior to stent insertion. After the procedure, the enrolled patients will be visited for evaluation and management of underlying diseases, routine assessments, and optimal medical therapy. Clinical follow-ups will be performed at 1, 3, 6, and 12 months and telephone contacts will be performed every month till the end of the study. An assessment of angina status, cardiovascular drug use, dyspnea, and any serious adverse events will be recorded during these clinical follow-up visits. Illustrative participant timeline is shown in Figs 1 and 2.

**Fig 2 pone.0325663.g002:**
[figure not shown]
The flow diagram of the study. *Optimal Medical Therapy refers to the best possible use of medical therapies to manage chronic conditions, particularly in cardiovascular diseases. In the context of coronary artery disease (CAD), OMT typically includes medications such as antiplatelets, statins, beta-blockers, and angiotensin-converting enzyme (ACE) inhibitors or angiotensin receptor blockers (ARBs), all aimed at reducing the risk of MACE.

### Sample size

This study is designed to compare 6- and 12-month ticagrelor monotherapy to the conventional DAPT treatment in terms of efficacy and safety. We hypothesize that ticagrelor monotherapy is non-inferior for safety and efficacy to the DAPT regimen. The null hypothesis is the superiority of the standard DAPT regimen for both safety and efficacy primary endpoint. Based on the results of the international trials (GLOBAL LEADERS, STOP-DAPT-2, and TICO trials) and related article in our country (19) we anticipate that 2% of patients in the control and treatment arm will reach the co-primary efficacy endpoint. The non-inferiority margin is assumed to be 50% of the mentioned cumulative incidence (1%). The level of significance (one-sided alpha) and power (1-β) of the study were considered 5% and 80% respectively. Based on these assumptions, 2424 patients are required for each arm of the ideal study. Taking into consideration of loss to follow-up cases (10%), we have to enroll 5400 patients with 1:1 randomization to each arm in the ideal study. The formula that has been used for these calculations is shown in Formula 1 (20). However, due to the limited number of cases referred to our center and the safety uncertainties of the project, we will first conduct the initial phase of the study. We estimated that a total of 400 patients would be referred to our center for CCS management over a three-month period (the expected recruitment time for initial phase). With the goal of reaching the target sample size within approximately three years, the suitable sample size for the initiation phase is calculated to be about 180 patients in each arm of the study using Formula 2.

**Fomula 1**: $\backslash (N=2\;\times \;{\left(\frac{Z_{1-\alpha }+Z_{1-\beta }}{\delta_{0}}\right)}^{2}\times p\;\times (1-p).\;\backslash )$ N = size per group; p = the response rate of standard treatment group; z(x)= the standard normal deviate for a one or two sided x; δ0 = a clinically acceptable margin

**Fomula 2**: $\backslash (n=\;\frac{n_{0}}{1+\;\frac{\left(n_{0}-1\right)}{N}}\;\backslash )$. n=suitable sample size for the study; n0=ideal sample size x; N= total patients available

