### Objective

Building on the background presented, we designed a randomized, two-arm, double-blinded trial aims to compare the safety and efficacy of **TICA**gre**L**or m**ON**otherapy versus DAPT in CCS patients post percutaneous coronary int**E**rvention (TICALONE). We hypothesize that immediate ticagrelor monotherapy (without the DAPT period) will be non-inferior to the conventional DAPT regimen and will provide comparable protection against ischemic events while offering a reduced bleeding risk. If confirmed, this study could influence future clinical guidelines and shift the current paradigm in post-PCI management for CCS patients. The TICALONE protocol was developed through the coordination of the [name] Clinic team and the **T**raditional and **A**dvanced **H**eart **A**pproaches clinical center, as their 10^th^ trial (TICALONE-TAHA10). It has been prepared in accordance with the guidelines outlined by the Standard Protocol Items: Recommendations for Interventional Trials (SPIRIT).

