### Statistical analysis

Continuous variables will be presented as mean ± SD and categorical variables will be presented as counts and percentages. The comparison of categorical variables will be conducted using either the χ² test or Fisher’s exact test. To compare continuous variables, the Student’s t-test or the Wilcoxon rank-sum test will be used for non-normally distributed data. The statistical analyses will be carried out using Stata version 18.0 (StataCorp LLC, College Station, Texas, USA). All primary and secondary endpoints will be analyzed both on an intention-to-treat basis, determined by allocation. Cumulative event rates will be estimated with the Kaplan-Meier method. The Cox log-rank approach will be utilized to compare the incidence of endpoints, specifically focusing on the time-to-first-event analyses. Patients lost to follow-up will be censored at the time of the last known contact. The null hypothesis will be evaluated on the intention-to-treat population using inferiority statistics. If the upper limit of the one-sided 95% confidence interval of the difference is less than the prespecified non-inferiority margin of 1%, ticagrelor monotherapy will be considered non-inferior to the conventional 6-month DAPT regimen. A subgroup analysis will be conducted for clinically relevant factors such as age, sex, comorbidities, prior use of aspirin or P2Y12 inhibitors, lesion or procedural characteristics, and other risk indicators. A two-sided test will be used for all hypotheses testing at a 5% significance level. The results of this study will be reported in accordance with CONSORT statement. Statistical analysis and reporting of trial results will follow the estimand framework [24].

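### Non-inferiority is hypothesised for efficacy and bleeding, but the rate, margin and sample size come from efficacy alone, so the 80% power covers efficacy only and bleeding has no margin of its own

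*Protocol article*

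**What the plan says.** The Sample size section of the protocol article states the hypothesis as "We hypothesize that ticagrelor monotherapy is non-inferior for safety and efficacy to the DAPT regimen" and the null as "The null hypothesis is the superiority of the standard DAPT regimen for both safety and efficacy primary endpoint". Outcomes makes BARC type 3 or 5 bleeding the primary safety endpoint and calls the efficacy composite co-primary.

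The planning figures concern one endpoint. The event rate is introduced with "we anticipate that 2% of patients in the control and treatment arm will reach the co-primary efficacy endpoint", and the margin is set at half of that incidence, which is 1 percentage point. The section continues "The level of significance (one-sided alpha) and power (1-β) of the study were considered 5% and 80% respectively" and concludes that "2424 patients are required for each arm of the ideal study". It gives no BARC 3 or 5 rate, bleeding margin or bleeding power.

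Under Statistical analysis, if the upper one-sided 95% limit of the difference lies below 1%, "ticagrelor monotherapy will be considered non-inferior to the conventional 6-month DAPT regimen". The endpoint whose difference is meant is not named.

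The Objective section adds to non-inferiority the expectation that the regimen "will provide comparable protection against ischemic events while offering a reduced bleeding risk".

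**The concern.** Bleeding is written into the confirmatory hypothesis, yet nothing in the planning supports a conclusion about it. Three things follow.

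- **Power.** A reader who takes the hypothesis and the power sentence together may credit the 80% to the two-endpoint claim. It can belong only to efficacy.
- **Margin.** The only margin in the article is half of an ischaemic event rate. If it is carried over to major bleeding, it may be very wide relative to the bleeding rate, and a clear excess of bleeds could be reported as non-inferior safety.
- **Objective.** The case for omitting aspirin rests on less bleeding. A non-inferiority test on bleeding could succeed without showing any reduction.

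**Working it through.** **Inputs from the Sample size section:** p = 0.02 in both arms, margin δ = 0.01, one-sided α = 0.05 (z = 1.645), power 0.80 (z = 0.842), 10% loss to follow-up. **Not in the documents:** any BARC 3 or 5 rate. Bleeding rates below are assumptions, shown over 0.5% to 3%.

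**1. Reproducing the stated size.** Formula 1, with efficacy inputs only:

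N = 2 × ((1.645 + 0.842)/0.01)² × 0.02 × 0.98 = 2,424 per arm, an exact match.

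Allowing for 10% loss, 2,424/0.9 rounds up to 2,694 per arm, or 5,388 in total, against the stated 5,400. No bleeding input is needed or used.

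**2. Power to meet both endpoints at 2,424 per arm.** Efficacy power is 80.0%. The chance of meeting two criteria cannot exceed the chance of meeting either one, so joint power is at most 80%. With equal true bleeding rates p and a 1-point margin:

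bleeding power = Φ(0.01/√(2p(1−p)/2424) − 1.645); joint power under independence = 0.80 × bleeding power.

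| Assumed bleeding rate, both arms | Bleeding power | Joint power |
|---|---|---|
| 0.5% | >99.9% | 80% |
| 1% | 96.8% | 77% |
| 1.5% | 88.9% | 71% |
| 2% | 80.0% | 64% |
| 3% | 65.4% | 52% |

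Independence is not critical: at 2%, joint power is 66.6% with correlation 0.3 and 62.6% with correlation −0.2.

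If bleeding is truly lower on ticagrelor, the loss nearly vanishes: 79.7% for 2% versus 1.4%, and 80.0% for 2% versus 1%.

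If the half-of-the-rate rule were applied to bleeding as well, joint power would be 43% at a 1% rate (margin 0.5 points) and 27% at 0.5% (margin 0.25 points).

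**3. What the 1% rule would accept if used for bleeding.** Assume control bleeding of about 0.5%, that is 12 of 2,424 (0.495%), against 26 of 2,424 (1.073%) on ticagrelor.

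- Difference: 0.578 points.
- Standard error: √(0.00495 × 0.99505/2424 + 0.01073 × 0.98927/2424) = 0.253 points.
- Upper one-sided 95% limit: 0.578 + 1.645 × 0.253 = 0.994 points, below 1, so the rule is met.
- Test of no difference: z = 0.578/0.253 = 2.28, two-sided p about 0.02 against ticagrelor.
- Ratio: 26/12 = 2.2.

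A statistically detectable doubling of major bleeding would be called non-inferior.

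**4. Power to show the reduction the Objective expects.** Superiority at two-sided 5% with 2,424 per arm has 82% power for 2% versus 1%, 52% for 1% versus 0.5%, and 37% for 2% versus 1.4%. The article specifies no superiority test for bleeding.

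**The case against.** The strongest reply is that the article never promises 80% joint power. The figure follows directly on the efficacy rate, and the size reproduces from efficacy alone. Any shortfall depends on bleeding rates the article does not give, and on its own expectation of less bleeding there is almost none. This stands: a reader might infer that a promised joint power has been missed, but the documents support only a ceiling of 80% that cannot be verified.

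Three other stronger readings also fail.

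- **That the Objective and the null contradict each other.** A true reduction in bleeding also satisfies non-inferiority. The two sections are mismatched rather than opposed.
- **That the one-sided error approaches 10%.** With two independent tests at 5%, 1 − 0.95² = 9.75%, but only if success on either endpoint suffices. No section states such a rule, and the wording points more naturally to both being required, which needs no split of alpha.
- **That 1.48% versus 1.00% bleeding would pass as non-inferior although clearly higher.** Its upper limit is 1.003 points, so it just fails, and its two-sided p is 0.13.

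Applying the 1% margin to bleeding is itself one reading of an ambiguous sentence, so the 12 versus 26 example is conditional on it. It is also fair that the trial first commits to about 180 per arm, where efficacy power is only 16.7%, so the 2,424 calculation concerns the full study.

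What a separate analysis plan might settle, such as the order of testing, is not the complaint. The defect lies in what the article states: a two-endpoint hypothesis, a one-endpoint calculation, and a decision rule without a named endpoint.

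**Conclusion.** The point holds in limited form. The two-endpoint hypothesis rests on planning figures for efficacy only: 2,424 per arm reproduces exactly without any bleeding input. The 80% power is therefore efficacy power. Power to meet both endpoints is at most 80% and, under equal arms, independence and a 1-point margin, runs from about 80% at an assumed 0.5% bleeding rate to 64% at 2% and 52% at 3%. The article gives no figure that selects among these.

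The more serious consequence is for the conclusion. If the unnamed difference includes bleeding, and control bleeding is near 0.5%, the rule would accept a 2.2-fold excess of major bleeds. The expected reduction in bleeding has no test that could establish it. This should be corrected, but it does not invalidate the efficacy calculation.

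**What to change.** In Sample size, state that the 80% power and the 1% margin refer to the efficacy composite only, and remove safety from the non-inferiority hypothesis and null. In Statistical analysis, name the efficacy composite as the endpoint to which the 1% rule applies. To match the Objective, test BARC 3 or 5 bleeding for superiority at two-sided 5% only after efficacy non-inferiority has been met, and say that this test is not separately powered.

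This is one option. If bleeding non-inferiority is to be kept, state an assumed BARC 3 or 5 rate and a margin justified for bleeding, require both endpoints to pass, and restate the joint power or the size. For example, with a 2% bleeding rate and a 1-point margin, 80% joint power needs 3,286 per arm, or 7,304 in total after 10% loss.

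The first option leaves the sample size unchanged. It costs a less favourable power statement for bleeding and, because it changes a stated hypothesis, a formal amendment with ethics committee approval under the article's Protocol amendments section.

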The fact that P2Y12 monotherapy have superior efficacy and similar safety compared to aspirin monotherapy align with the current guidelines recommendations that prioritize the discontinuation of aspirin to discontinuation of P2Y12 inhibitor [21,30]. Choosing the appropriate P2Y12 inhibitor as an alternative to DAPT required a careful evaluation of the benefits and side effects of each drug. A previous meta-analysis revealed no significant difference between ticagrelor and Prasugrel in their effects on ACS patients [31]. However, research on prasugrel is more limited, and it is less widely available in global markets. The mentioned meta-analysis also demonstrated that, compared to clopidogrel, ticagrelor significantly reduced both all-cause mortality and CV deaths. We recognize that a major drawback of ticagrelor is reduced treatment compliance due to the dyspnea it can cause. To address this, we will closely monitor patients during follow-up visits to assess any occurrences of dyspnea and will report its prevalence among study participants.

The elimination of aspirin as the backbone of current regimens may lead to unforeseen adverse events and complications. For this reason, we designed the TICALONE trial to begin with an initiation phase involving 360 participants, followed by a 6- and 12-month follow-up. After releasing the initial results, we will evaluate whether to continue the trial as planned to reach the ultimate sample size or to make adjustments to the trial design. This approach allows us to refine the study in order to achieve the best outcomes and contribute to determining the most appropriate post-PCI regimen for CCS patients. We designed this trial with a 12-month follow-up, but longer-term evaluation and assessment of CCS patients are necessary to determine the most suitable regimen after PCI. We look forward to the initial results, which will guide the continuation of the study and help the TICALONE team develop the most accurate recommendations for updating clinical guidelines.

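### The initial-phase size of about 180 per arm is justified by a finite-population correction that does not apply to a randomised comparison; its power for the 1-point margin is about 17%, which is not stated, and the phase is not exempted from the non-inferiority rule

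*Protocol article*

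**What the plan says.** In the protocol article, Sample size sets the design inputs: "we anticipate that 2% of patients in the control and treatment arm will reach the co-primary efficacy endpoint", a margin of half that rate (1 percentage point), and "The level of significance (one-sided alpha) and power (1-β) of the study were considered 5% and 80% respectively". Formula 1 then gives 2424 per arm, raised to 5400 in total for 10% loss. The article calls this the ideal study.

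The same section turns to a first phase, giving limited referrals and safety uncertainty as the reasons. It expects 400 referrals in three months and states that "the suitable sample size for the initiation phase is calculated to be about 180 patients in each arm of the study using Formula 2". Formula 2 is n = n0 / (1 + (n0 − 1)/N), with the key "n=suitable sample size for the study; n0=ideal sample size x; N= total patients available". No power or precision is given for the reduced size.

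Statistical analysis holds one decision rule, with no restriction to the full-size trial: "If the upper limit of the one-sided 95% confidence interval of the difference is less than the prespecified non-inferiority margin of 1" per cent, ticagrelor monotherapy is to be considered non-inferior. The Discussion says "we designed the TICALONE trial to begin with an initiation phase involving 360 participants", with continuation or redesign to be considered once the first results are out. Trial results (Dissemination policy) and Trial status plan publication after 6 and 12 months of follow-up.

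**The concern.** A finite-population correction reduces a sample when the aim is to describe one fixed, finite group sampled without replacement. As the sample approaches the whole group, the sampling error goes to zero. A randomised comparison has a different aim and a different source of error. The trial wants to inform the treatment of future patients, and each patient is seen under one treatment only. The error of the difference depends on patients and events per arm, not on how many patients one centre expects in a quarter.

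The reduced size therefore does not inherit the properties of the 2424 per arm it is computed from. Because the text presents 180 as calculated from the ideal size, and the only power figure in the article is 80%, the loss of power is not visible. What is at stake is how the first published results on an immediate aspirin-free regimen are read. With so few events, a failure to show non-inferiority would say little, and a pass would depend largely on chance. Both could be reported under a rule sized for thirteen times as many patients (2424/180 = 13.5).

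**Working it through.** **Inputs** (Sample size): event rate p = 0.02 in both arms; margin 0.01; one-sided alpha 0.05 (z = 1.645); power 0.80 (z = 0.842); N = 400; 180 per arm; 10% loss.

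**1. The plan's Formula 1.** 2 × ((1.645 + 0.842)/0.01)² × 0.02 × 0.98 ≈ 2424 per arm. This reproduces the stated figure.

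**2. The plan's Formula 2, N = 400.** The article does not say which n0 was used.

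| n0 | Formula 2, total | per arm |
|---|---|---|
| 2424 | 343.5 | 171.7 |
| 2700 | 348.5 | 174.2 |
| 4848 (2 × 2424) | 369.6 | 184.8 |
| 5400 | 372.5 | 186.2 |

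For example, 4848/(1 + 4847/400) = 4848/13.1175 = 369.6. The candidates lie on both sides of 180, and 184.8 is within 3% of it. The stated figure of about 180 is reproduced.

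**3. How Formula 2 responds to the design target.** Take n0 as twice the Formula 1 size. Then 80% power gives a total of 370, 90% gives 378 and 99% gives 387. As n0 grows, the formula tends to N = 400 and never passes it. The output restates availability and hardly depends on power.

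**4. Enrolling all 400.** The correction would imply no remaining sampling error. With 200 per arm, the standard error of the difference is √(2 × 0.0196/200) = 1.40 points, and power is Φ(0.01/0.0140 − 1.645) = Φ(−0.931) ≈ 17.6%.

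**5. Power at the planned size.** SE = √(2 × 0.02 × 0.98/n) and power = Φ(0.01/SE − 1.645).

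- n = 180: SE = 1.476 points; power = Φ(0.678 − 1.645) = 16.7%.
- n = 162 (180 × 0.9): SE = 1.556 points; power = 15.8%.
- n = 2424: SE = 0.402 points; power = 80.0%.

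Exact binomial enumeration gives 16.7% (Wald limit) or 14.2% (Newcombe limit) at 180 per arm, and 17.7% or 11.6% at 162. Statistical analysis also has a sentence setting two-sided 5% tests throughout. If that governed the non-inferiority test (one-sided 2.5%), the normal approximation gives 10.0% at 180 per arm.

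**6. What this means in events.** Expected events are 180 × 0.02 = 3.6 per arm. The one-sided 95% limit lies 1.645 × 1.476 = 2.4 points above the observed difference at 2% rates. With Wald limits at 180 per arm, ticagrelor first:

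- 4 vs 4 events: upper limit 2.6%, fails.
- 2 vs 4: upper limit 1.1%, fails.
- 1 vs 4: upper limit 0.4%, passes.

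**7. Margin at which 180 per arm has 80% power.** (1.645 + 0.842) × 1.476 = 3.7 points, against the planned 1 point.

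**The case against.** The strongest defence is that the article does not offer the first phase as a powered trial. It attaches 80% to the ideal study of 2424 per arm, gives limited referrals and safety uncertainty as the reasons for starting small, and says the first results will guide continuation or redesign. A separate analysis for this phase may also stand in a full protocol or analysis plan that is not shown. This stands, and it limits the point. It does not rescue Formula 2, which the article itself states as the calculation behind the size.

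Some stronger readings are tempting, and the document does not support them.

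- A reader might infer that 80% power is claimed for the 360 patients. No sentence says so.
- A reader might infer that the 1% rule will certainly be applied to them. That is only an inference from one unrestricted rule together with the publication plans. The exact statement is that the article does not exempt the phase.
- A reader might take 180 for an arithmetic slip. It is not: Formula 2 gives about that number. The method is wrong, not the sum.
- From the 2.4-point distance to the limit, a reader might conclude that ticagrelor must be observed at least 1.4 points better to pass, or that the phase is almost sure to be inconclusive. The distance shrinks when events are few: 1 vs 3 passes at 1.11 points better (upper limit 0.70%), and 0 vs 1 passes at 0.56 points (0.36%). A chance of about one in six is low, not negligible.
- A reader might conclude that the target stated in "With the goal of reaching the target sample size within approximately three years" cannot be met. At 400 per three months, three years give 400 × 12 = 4800, below 5400. But Recruitment gives 100 to 200 procedures a month, or 3600 to 7200 over 36 months, and 5400 needs 150 a month. The two figures need reconciling; failure is not shown.

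**Conclusion.** The point holds in this form: Formula 2 is not a valid basis for the size of a randomised two-arm phase, and the size it is used to justify has about 17% power for the plan's own margin (about 16% after 10% loss by the same approximation), against 80% for the full-size trial. The power figure assumes true rates of 2% in both arms, the one-sided 5% level in Sample size, and the confidence-limit rule in Statistical analysis. With the exact methods or the stricter one-sided 2.5% level it stays low. The article states no power for the phase and does not separate it from the 1% rule. This must be corrected, because a stated sample-size calculation is wrong as written and the results it governs are to be published. The phase itself may be reasonable as a feasibility and safety step; nothing here argues against its size on those grounds.

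**What to change.** - In Sample size, delete Formula 2 and the statement that 180 per arm is calculated from it. Say that about 180 per arm is set by feasibility, and that its power for the 1-point margin is about 17% (about 16% with 10% loss) at 2% event rates and one-sided 5%.
- In Statistical analysis, state that the initial phase is reported as event rates and differences with confidence intervals, without a non-inferiority conclusion, and that the 1% rule is reserved for the full-size trial of 2424 evaluable patients per arm. Carry the same distinction into the Discussion and Trial results.
- As a minor addition, reconcile the 400 referrals per three months in Sample size and the 100 to 200 procedures a month in Recruitment with the three-year target of 5400.

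The cost is protocol wording only, with no extra patients. The price is that the initial phase can no longer claim non-inferiority.
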